## Abstract

**Background:**

Increasingly, strength-based approaches to health and wellbeing interventions with Aboriginal and Torres Strait Islander Australians are being explored. This is a welcome counter to deficit-based initiatives which can represent a non-Indigenous view of outcomes of interest. However, the evidence base is not well developed. This paper presents the protocol for evaluating a strengths-based initiative which provides life coaching services to Aboriginal and Torres Strait Islander community housing tenants. The study aims to evaluate the effect of life coaching on social and emotional wellbeing (SEWB) of tenants in three Victorian regions.

**Methods:**

The More Than a Landlord (MTAL) study is a prospective cohort study of Aboriginal Housing Victoria tenants aged 16 years and over that embeds the evaluation of a life coaching program. All tenant holders in one metropolitan and two regional areas of Victoria are invited to participate in a survey of SEWB, containing items consistent with key categories of SEWB as understood and defined by Aboriginal and Torres Strait Islander peoples, and key demographics, administered by Aboriginal and Torres Strait Islander peer researchers at baseline, 6 and 18 months. Survey participants are then invited to participate in strengths based life coaching, using the GROW model, for a duration of up to 18 months. Indigenous life coaches provide tenants with structured support in identifying and making progress towards their goals and aspirations, rather than needs. The study aims to recruit a minimum of 200 survey participants of which it is anticipated that approximately 73% will agree to life coaching.

**Discussion:**

The MTAL study is a response to Aboriginal and Torres Strait Islander community and organisational requests to build the evidence base for an initiative originally developed and piloted within an Aboriginal controlled organisation. The study design aligns with key principles for research in Indigenous communities in promoting control, decision making and capacity building. The MTAL study will provide essential evidence to evaluate the effectiveness of strengths-based initiatives in promoting SEWB in these communities and provide new evidence about the relationship between strengths, resilience, self-determination and wellbeing outcomes.

**Trial registration:**

This trial was retrospectively registered with the ISRCTN Register on the 12/7/21 with the study ID:ISRCTN33665735.

## Background

Aboriginal and Torres Strait Islander peoples have inhabited Australia, for over 65,000 years [1]. Aboriginal and Torres Strait Islander peoples have, over time, developed complex societies, knowledges and cultures. Sophisticated local knowledge systems in pharmaceuticals, ecology, geography, farming and social systems along with spiritual and artistic endeavours are just a few of the skills that have enabled Aboriginal and Torres Strait Islander peoples to adapt and thrive in changing environmental conditions prior to colonisation [2, 3].

Aboriginal and Torres Strait Islander knowledges inform a broad and holistic understanding of health and wellbeing that encompasses mental, physical, cultural and spiritual health [4]. The term social and emotional wellbeing (SEWB) is used in this study to describe the health and wellbeing of Aboriginal and Torres Strait Islander peoples. In this context, SEWB describes a ‘physically healthy, culturally intact and spiritually connected person’ ([5] p.9). The term captures the way in which Aboriginal and Torres Strait Islander people view the need for a multiplicity of elements to be in balance at both a community and individual level to achieve health and wellbeing [4–7]. Gee et al. [8] have identified seven elements of Aboriginal and Torres Strait Islander social and emotional wellbeing (SEWB); these include connection to body; mind and emotions; family and kinship; community; culture; country; and spirit, spirituality and ancestors. These elements of wellbeing for Aboriginal and Torres Strait Islander people, families and communities are influenced by broader historical, political and social determinants of health. For example, against the backdrop of colonisation the extent to which communities have managed to maintain cultural continuity, self-determination and community control, will in turn shape environments that people are born into with regards to family/community stability, cohesion and wellbeing - or conversely, historical/cultural loss and social disadvantage.

For many, colonisation has seen the destruction or fragmentation of family and community, traditional lands, languages and cultural practices [9]. These are key elements of SEWB and such losses have, in many cases, resulted in profound trauma for Aboriginal and Torres Strait Islander peoples [10]. The strength, resilience and political will of Aboriginal and Torres Strait Islander peoples have enabled their survival. However, trauma associated with colonisation, assimilation practices, forced removal, ongoing structural inequities and racism persist [11]. The impact of trauma is reflected in high rates of unemployment, incarceration, substandard, insecure and overcrowded housing, rates of chronic disease, mental health conditions, suicide and hospitalisation [12–15]. Yet, these statistics only paint part of the picture.

Much research, government discourse and supporting data has had a focus on ‘difference, disparity, disadvantage, dysfunction and deprivation’ of Aboriginal and Torres Strait Islander people compared to non-Indigenous populations ( [16] p.235). As Walter and Suina [16] argue, this representation is informed by the world view of the researcher, historically a non-Indigenous worldview. While, there is a need to acknowledge the extent of disadvantage experienced by Aboriginal and Torres Strait Islander people, when this becomes the dominant narrative, it excludes alternative approaches to thinking about Aboriginal and Torres Strait Islander health and wellbeing [17]. Deficit-based approaches have consistently failed to address the current challenges experienced by Aboriginal and Torres Strait Islander peoples. In particular, they often do not adequately address and strengthen key elements of SEWB, as previously defined.

Strengths based approaches to research with Aboriginal and Torres Strait Islander people have increasingly attracted attention (see for example [18–20]). Such approaches are drawn from multiple sources, including the field of positive psychology [17]. Strengths are positive capabilities, found in individuals, which support development, growth and the attainment of goals [21]. A strengths based approach is based on the premise that inherent strengths and resilience can by unlocked with structured support. This approach recognises that individuals live within families, communities and a culture that also have strengths and resources that will contribute to wellbeing [22]. The process involves, in collaboration with a practitioner, developing self-determined goals, identifying opportunities, capabilities and assets that foster progress and growth, examining what is going well and building on it. The aim is to raise awareness of and cultivate identified strengths and assist individuals in transferring learnings to other areas of their lives and create growth for the family unit as a whole [23, 24].

Extensive national consultations with Aboriginal and Torres Strait Islander communities have identified the need to recognise collective strengths such as connection to culture and kinship systems, and resistance and commitment to unresolved social justice issues (e.g., dispossession of land, racism). Hence, strength-based approaches align with principles of Aboriginal and Torres Strait Islander empowerment, healing and self-determination [25]. They are also seen as a counter to deficit-based discourse [26].

Concurrently, critiques of strengths-based approaches warn against shifting responsibility for structural inequities to the local and individual level [27]. Further critiques highlight the western ethnocentric individualistic nature of strengths based approaches that attempt to universalise construction of self and behaviour [10, 28]. In light of these critiques, Aboriginal and Torres Strait Islander perspectives are central to adopting strength-based approaches within these communities. Specific strengths and outcomes valued by Aboriginal and Torres Strait Islander people need to be addressed.

This paper outlines the design and methods to be used in an evaluation study of a strengths-based approach to improving the SEWB of tenants of Aboriginal Housing Victoria (AHV), embedded within a prospective cohort study. This study builds on an earlier AHV pilot of a life coaching service informed by a household survey developed with families who had AHV tenancies. The pilot study addressed the SEWB of tenants by supporting their aspirations rather than needs. Aspirations were fed back to AHV and enabled life-coaches to engage with tenants to make aspiration plans and to connect tenants with appropriate services and local programs aligned to their goals. The strengths-based pilot focused on empowerment and self-determination. The pilot study provided important data to inform and influence AHV housing policy, decisions and service response. The current study, known as More Than a Landlord (MTAL), has been developed in response to calls from Aboriginal and Torres Strait Islander people and providers locally and more broadly for a rigorous evidence base to be developed through evaluation to underpin the life coaching service.

## Methods/design

This research aims to evaluate the effect of a regionally tailored, Indigenous-led life-coaching service on the SEWB of Indigenous people in three regions of Victoria. The evaluation study will be conducted in two parts examining the implementation of life coaching using qualitative and quantitative methods. Part one is an observational study of SEWB, physical health, housing, education, and financial wellbeing, using self-reported measures in a survey completed by Aboriginal and Torres Strait Islander people who are tenants of AHV who adopt life coaching and those who do not. Part two is a complimentary qualitative and quantitative study that seeks to understand the experience and impact of life coaching on tenants through a periodic pulse check and an interview. The study will contribute to building the evidence base for strengths-based initiatives in improving the SEWB of Aboriginal and Torres Strait Islander people.

MTAL is overseen by a governance group of chief investigators and AHV representatives who meet periodically. A memorandum of understanding was developed between AHV and the University of Melbourne and reviewed by the AHV board before sign off.

### Study population

This study is conducted in partnership with AHV, which is an Aboriginal community organisation responsible for managing over 1500 rental properties for Aboriginal and Torres Strait Islander people living in Victoria, Australia. AHV has identified three regions in which the study will be conducted: North west metropolitan Melbourne and two regional areas; Ballarat and the greater Geelong area. The regions were selected by AHV based on data that indicated that the population of tenants in the regions experienced more stability in managing tenancies (e.g. fewer issues with rental payments) and may be more able to participate in life coaching. All Aboriginal and Torres Strait Islander people aged 16 years and over, who are tenants of AHV and reside in the three regions are eligible to participate. There will be three main groups of people in the research, those who decline to be surveyed, survey participants (Part 1 sample), and a subset of survey participants who become life coaching participants (Part 2 sample) as shown in Fig. 1.

**Fig. 1 Fig1:**
[figure not shown]
Participants type and anticipated numbers

Based on the uptake in the pilot survey, of the 389 tenant holders we approach in the three regions, we are anticipating that a minimum of 51% will agree to the survey. We are expecting 146 of the 200 tenant holders surveyed (73%) to continue on to life coaching. There may be additional tenants in each household recruited to the life coaching and/or survey.

### Recruitment

This section outlines the approach to recruiting study participants, and recruiting and training peer researchers and life coaches.

#### Survey and life coaching participants

Prior to recruitment, the study will be publicised through existing AHV channels such as newsletters and community events and modified to meet the requirements of COVID-19 restrictions. All named tenant holders of AHV tenancies in the three participating regions will be contacted by phone by Aboriginal and Torres Strait Islander peer researchers and invited to participate in three surveys of SEWB at baseline, 6 months and 18 months. An appointment will be made to provide and explain the survey plain language statement, obtain written informed consent and undertake the baseline survey with those agreeing to participate. This appointment may be face to face, by phone or virtually via video link.

After completing the survey, participants will be offered life coaching. Survey participants interested in undertaking life coaching will be contacted by an Aboriginal or Torres Strait Islander life coach to explain the life coaching program and make an appointment. This appointment will be face to face, unless COVID-19 restrictions require the use of phone or videolink. The life coach will provide and explain the life coaching plain language statement, obtain written informed consent and commence life coaching with those agreeing to participate.

#### Peer researchers

Approximately 10 Aboriginal or Torres Strait Islander peer researchers will be recruited by AHV from the AHV tenant population in the three regions. Drawing peer researchers from local communities is an important element of the study in both facilitating better participant engagement in the surveys and strengthening community capacity.

Positions will be advertised in AHV newsletters and through community events. An information pack will be made available to all potential applicants and will include information on the project, work expectations and the application process. Successful applicants will then be provided with a 1 week training program in research, ethics and consent, confidentiality, communicating the research to participants, contacting participants, conducting the survey, use of survey technology, participant distress protocols and preparation for work. Throughout the survey periods, peer researchers will meet weekly with a peer researcher coordinator to schedule appointments, discuss issues, problem solve and undertake any additional training.

#### Life coaches

Aboriginal and Torres Strait Islander life coaches will comprise existing AHV life coaching staff and newly recruited staff. Recruitment will target individuals with a relevant qualification in community development, health/wellbeing or life coaching. All staff will undertake a one-week course providing them with essential tools for life coaching. Training will cover coaching models, dealing with challenging conversations, developing goals and actions, cultural determinants of SEWB, introduction to research and data collection, relationship building and self-care. The training is similar in content to accredited life coaching courses, at an introductory level, and tailored to be culturally appropriate and address research requirements. The life coaches will also attend the peer researcher training.

### Study components

The MTAL study consists of the following main components: development, the life coaching intervention and data collection. These study activities are described in this section and presented in the timeline in Fig. 2.

**Fig. 2 Fig2:**
[figure not shown]
Timeline of study activites

#### Development

The initial development phase consists of developing data collection tools and processes and training for peer researchers and life coaches. A survey was developed to examine SEWB in part one of the study. Data collection tools, developed for part two of the study, capture the experience and impact of life coaching and information about strengths identified, include the support plan, pulse check and a qualitative interview.

#### Life coaching intervention

The approach to life coaching will be based on the GROW (Goal, Reality, Options, Will) model [29] and motivational interviewing [30]. Life coaches will meet with life coaching participants in weekly face to face sessions for the first 4 weeks. After that, contact will be approximately fortnightly for a duration of up to 18 months via a range of formats including face to face, text, email, phone call and video link.

In the early stages life coaches will assist participants to identify and prioritise goals and identify actions required to meet goals. Life coaches will use questions derived from the GROW model to assist participants in identifying a goal they wish to work on, resources and barriers, possible actions to achieving their goal and their motivation to change [29]. Goals and actions will be documented on an electronic support plan at least every 3 months. Progress with reaching goal/s will be discussed at every session and every 3 months the life coach will update the support plan and administer a pulse check, which will prompt the tenant to reflect on their progress and their strengths. The aim of life coaching is to raise a tenant’s awareness of the strengths they possess and the resources available in the community to achieve desired changes in their life. People who have knowledge of and use their strengths has been shown to experience greater wellbeing [21]. Life coaches will meet regularly with the life coach coordinator to discuss individual coaching interventions and coaching approaches. The life coaching intervention is summarised in Fig. 3.

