#### Survey

The MTAL survey, including items examining SEWB, was initially developed and used as part of an Indigenous led First 1000 days Australia initiative to describe the aspirations and needs of Aboriginal and Torres Strait Islander families [31]. The survey was modified to meet the needs of the MTAL project and piloted by an Aboriginal controlled health and community service in the eastern region of Melbourne with 22 local community members. The survey was then tailored to the AHV context by AHV staff and researchers to reflect the shift in focus from parenting to people who are tenants of AHV. The revised survey was piloted with five Aboriginal and Torres Strait Islander AHV staff. In addition to demographic information (age, Aboriginal and Torres Strait Islander identification, relationship status, postcode) the survey consists of 12 domains as outlined in Table 1.

**Table 1 Tab1:** Data collection

Data Type	Domain	Key measures
Survey	Education, Employment & Finances	Highest level of education completed, employment status, barriers to employment, spending, bill payments, bill stress
	Family	Number of children birthed/adopted/cared for, dependents/age/relationship**,** Strengths-based parenting tool [32]
	Out of Home Care	Removals/child protection services, age of housing independence, cultural placement plan
	Culture and Community	Connection to culture and community, community attitudes
	Cultural safety	Unfair treatment, unsafe environments
	Service Use	Service use and availability
	Self determination	Choice and control in decision making on issues
	Health	Health Conditions, Euroqual 5D -5 L [33], disability, smoking
	Wellbeing	Kessler-5 [34], Mental Health Continuum [35], Aboriginal Resilience and Recovery Questionnaire [9]
	Housing	Number and type of occupants, household amenities, financial stress due to tenancy
	Family violence	Experience of controlling, unsafe or threatening behaviour [36]
	Goal setting questions	Key categories of goals/aspirations
Pulse Check	Strengths	Key strengths used
	Resources	Use of community resources
	Resilience	Self-efficacy questions from Aboriginal Resilience and Recovery Questionnaire [9] and help seeking question
	Life coaching	Description of experience and impact of life coaching
Support Plan	Goals and actions	Number and type of goal/s, number of action/s, goals and actions achieved/partially achieved/not achieved
Interview	Life coaching	Experience and impact of life coaching

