### Statistical analysis

#### Representativeness of study participants

The data analysis will initially involve comparisons to determine the representativeness of the study participants. The first comparison involves examining whether the participants in the initial survey are representative both of all tenants in each of the three regions and of the full tenant population of AHV. AHV administrative data items will be compared for survey and non-survey participants. This comparison will guide the extent to which study findings could be generalised to the population of AHV tenants or tenants in other settings.

The second comparison examines the comparability between participants in the life coaching program and survey participants who declined life coaching. Comprehensive survey data will be used to explore differences between these two groups that could influence outcomes and potentially confound the estimated difference in outcomes between life coaching participants and those who declined. Potential confounders specified a priori will include education level, life stage, employment status, financial stress, family violence, childhood removal from natural family, out of home care, health and wellbeing, housing stability (e.g. absence of rent in arrears) and connection to community and family.

All comparisons will be made using linear and logistic regression for continuous and binary outcomes respectively. Robust estimation will be used to account for the clustering structure within the study, according to similarity (non-independence) of outcomes between people within a region and similarity of outcomes between people receiving life coaching from the same life coach.

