#### Outcome comparisons and SEWB over the period of life coaching

The final comparison compares the SEWB of life coaching participants with non-participants. The assessment of outcomes will be made by analysing a range of outcome variables reflecting the holistic nature of SEWB as defined earlier. Several aspects of the program delivery are hypothesised to bring about changes in the SEWB of life coaching participants. These include the total hours spent in life coaching, the period of life coaching, the number of and degree to which participants achieve goals and their related actions. It is anticipated that the type of goal chosen will influence which outcomes variable may change. For example, a goal to improve financial resources would likely result in a reduction in financial stress and perhaps an improvement in wellbeing but may have less impact on other outcomes such as connection to culture.

The predictor and outcome variables of interest are shown in Table 2.

**Table 2 Tab2:** Predictor and outcome variables

Predictor variables	Outcome variables
Period of life coaching (months)	Employment status
Exposure/dose of life coaching (hours)	Financial stress
Type of goal (category e.g., financial, employment)	Strengths based parenting
Number of goals (not achieved/partially achieved /achieved)	Connection to culture
Number of actions (not achieved/partially achieved/achieved)	Service use
	Health
	Wellbeing - resilience, psychological distress and mental health

Given the non-randomised design, adjusted analyses will be conducted to delineate whether any observed differential outcomes are due to coaching or could be accounted for by initial differences between the people who chose or declined to participate in life coaching. Comparisons will be adjusted for confounders specified a priori (as above) as well as baseline measure corresponding to the outcome under consideration.

For outcomes measured on a continuum (Euroqual 5D-5L, Kessler-5, Mental Health Continuum, and Aboriginal Resilience and Recovery Questionnaire) multilevel growth models [42] will be used to examine within-person change over time within individuals and communities in each region. The models will be extended to examine the effects of family contexts on the growth curves including individual, family and community level social determinants as measured in the surveys.

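### Coaching is self-selected, but neither the a priori confounders nor the key baseline measures include readiness to change, so the claim made for adjustment is too strong

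*Protocol article*

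**What the plan says.** All quotes are from the protocol article.

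- **Order of events** (Survey and life coaching participants): "After completing the survey, participants will be offered life coaching". Acceptors and decliners have therefore both completed the baseline survey before they choose.
- **Where motivation appears** (Life coaching intervention): the programme uses the GROW model and motivational interviewing. Coaches' questions help the tenant identify a goal, resources and barriers, "possible actions to achieving their goal and their motivation to change". This happens after the tenant has joined.
- **Confounders** (Representativeness of study participants): the list opens "Potential confounders specified a priori will include education level, life stage, employment status, financial stress, family violence, childhood removal from natural family", goes on to out-of-home care, and ends with "health and wellbeing, housing stability (e.g. absence of rent in arrears) and connection to community and family".
- **Baseline measures** (Survey, Table 1): the goal-setting section is described as "Key categories of goals/aspirations". Self determination and the Aboriginal Resilience and Recovery Questionnaire are also in the survey. The pulse check row adds self-efficacy questions from that questionnaire and a help-seeking question; the pulse check is given by coaches every 3 months.
- **Adjustment** (Outcome comparisons and SEWB over the period of life coaching): "Comparisons will be adjusted for confounders specified a priori (as above) as well as baseline measure corresponding to the outcome under consideration". The stated purpose is that "adjusted analyses will be conducted to delineate whether any observed differential outcomes are due to coaching or could be accounted for by initial differences" between those who chose coaching and those who declined it.

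**The concern.** The exposure is a decision to enter a goal-setting programme. Someone ready to make changes is more likely to accept the offer and may also improve without a coach. A characteristic that affects both uptake and later change confounds the contrast unless it, or something close to it, is measured in both groups and adjusted for.

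Adjusting for the baseline value of an outcome removes differences in starting level. It does not remove differences in the change that would have happened anyway, which is where readiness would act. If readiness is recorded only inside the coaching sessions, decliners have no value for it, and no later analysis can supply one. Part of any improvement due to willingness to change may then be read as an effect of coaching. This matters because the Discussion says the results will be used to advocate for interventions of this type with communities and funders.

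**Working it through.** **1. Is readiness in the stated adjustment set?**

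| Place | Readiness or motivation? | Who provides it |
|---|---|---|
| A priori confounder list | Not named | Both groups |
| Baseline survey, goal-setting section | Categories of goal only | Both groups |
| Baseline survey, self determination | Partial proxy; not in the confounder list | Both groups |
| Baseline survey, resilience questionnaire (has self-efficacy items) | Partial proxy; falls in the wellbeing domain, and health and wellbeing is a listed confounder | Both groups |
| Pulse check, help-seeking question | Related trait | Coached only |
| Coaching sessions | Motivation to change | Coached only |

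Motivation itself is described only for the coached group. Partial proxies exist for both groups, but only the resilience questionnaire falls within a listed confounder domain.

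**2. The plan's own figures.** 389 × 0.51 = 198.4, against about 200 expected in the survey; 200 × 0.73 = 146 coached, exactly. Declining: 200 − 146 = 54. The article states no alpha, effect size or SD, so there is no power calculation to reproduce.

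**3. Illustrative size.** Everything except the group sizes is an assumption.

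- Bias = d × g, where d is the gap in readiness between groups (assumed 0.3 to 0.8 SD) and g is the effect on the 18-month score per SD of readiness after the other adjustment (assumed 0.1 to 0.3 SD).
- Low: 0.3 × 0.1 = 0.03 SD. Middle: 0.5 × 0.2 = 0.10 SD. High: 0.8 × 0.3 = 0.24 SD.
- SE with assumed residual variance 0.64: √(0.64 × (1/146 + 1/54)) = 0.127 SD. With residual variance 1: √(1/146 + 1/54) = 0.159 SD. With 110 and 40 followed up (assumed) and variance 0.64: 0.148 SD.
- False-positive rate of a two-sided 5% test when coaching has no effect: P(|Z + bias/SE| > 1.96).

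| Bias (SD) | SE 0.127 | SE 0.148 | SE 0.159 |
|---|---|---|---|
| 0.03 | 5.6% | 5.5% | 5.4% |
| 0.10 | 12.3% | 10.4% | 9.6% |
| 0.24 | 47.0% | 36.9% | 32.5% |

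**4. If the proxies remove half the bias** (assumed; SE 0.127): 0.015 SD gives 5.2%, 0.05 SD gives 6.8% and 0.12 SD gives 15.6%.

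These SEs ignore clustering by region and coach, and the correlation between uptake and the covariates. Both would probably enlarge the SE. That would lower these rates but leave the bias itself unchanged.

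**The case against.** **The document names a different driver of engagement.** The Discussion says tenants with more stable lives are better able to engage, and the regions were chosen on similar grounds. Housing stability and financial stress are both on the confounder list. A reader might infer that motivation is the trait most likely to decide uptake; the document does not say so. What remains is that stability concerns ability to take part. Willingness is a separate reason for accepting, and the list does not name it.

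**Proxies are collected before the offer.** This stands. A reader might infer that motivation cannot be adjusted for and that its effect will certainly be credited to coaching. Both go too far: partial adjustment is possible with the survey as described, and a direct item could be asked of both groups. But self-efficacy is not readiness, and the self determination and goal responses are not in the stated adjustment set.

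**The article is condensed.** Table 1 lists key measures only, the confounder list is introduced with wording that allows additions, and the questionnaire is not shown. It may contain more. The point is therefore limited to the stated list and to the claim attached to it.

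**Any self-selected cohort has residual confounding, and the article acknowledges its non-randomised design.** True. The point is more specific: a characteristic that the programme itself works on is described only for coached tenants, while adjustment is said to distinguish coaching from initial differences in general.

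**Benefit on outcomes that a tenant's goals do not target might be read as a sign of self-selection.** The document does not support that check. It expects that a financial goal may also improve wellbeing, so such spillover could be a genuine effect.

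**Conclusion.** The point holds in limited form. Readiness or motivation to change is in neither the stated confounder list nor the key baseline measures, although coaching is self-selected. The description of coaching content is not itself an error. What needs correcting is the confounder list, together with the claim that adjustment can separate coaching from initial differences.

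Residual confounding by willingness to change is plausible and would probably favour coaching. Its size is not settled: 0.03 to 0.24 SD under the assumed inputs, with false-positive rates from about 5% to 47%, and less if the proxies work. The range includes negligible bias, so these figures show only that the problem could matter. The direction rests on the assumption that readier tenants both accept more often and improve more without coaching.

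**What to change.** 1. Add one or two readiness-to-change items to the goal-setting section of the baseline survey, asked of everyone before coaching is offered, and add them to the a priori confounder list.
2. For tenants already surveyed, name the collected proxies in the adjustment set: self determination, the goal-setting responses, and the self-efficacy items of the resilience questionnaire.
3. For each positive result, report how strongly an unmeasured confounder would have to be related to both uptake and outcome to remove it.
4. Reword the statement of purpose in the outcome comparisons section to say that adjustment covers measured initial differences only.

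The cost is a slightly longer survey and a little more analysis. Both groups answer the new items, so any effect of being asked is shared. If baseline surveys are already complete, steps 2 to 4 remain available.
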